### Health-economic evaluation

The economic analysis will be in the form of a service-utilization cost and consequences analysis. The costing will be undertaken as follows;

1) All resources used in delivering the intervention will be recorded prospectively and valued using standard methods [46] with unit costs provided by the study sites. Resource inputs would include:

(i) Time input of (a) the applicants to train/supervise the clinical psychologists implementing and supervising the intervention, (b) the clinical psychologists in training and supervising the day service lay therapists running the groups, (c) the day service lay therapists in running the groups, (d) administrative/secretarial staff attributable to the intervention.

(ii) Travel costs attributable to the intervention.

(iii) Consumable costs attributable to the intervention (e.g. production of manuals).

2) All other resources used by study participants at the intervention sites, and all resources used by study participants at control sites will be monitored prospectively, using recording logs overseen by the research team. These will be valued using standard methods with unit costs provided by the study sites.

3) All relevant resource use, apart from that at the study sites, will be collected at baseline and at follow-up using the Client Service Receipt Inventory (CSRI). The CSRI is a validated tool to measure total package resource use and has been used in evaluations involving service users with psychiatric problems and service users with learning disabilities [47,48]. It records items such as contacts with community-based primary care, other health or social services, educational services, outpatient and inpatient attendances, etc. Unit costs for most of these are available [49]. Information will be collected from service-users' key-workers and/or home carers for the three-month period immediately preceding data collection.

In relation to (2) and (3) above, we propose specifically to investigate staff allocation within the provided services. Service managers will be interviewed to ascertain the staff-to-service-user ratios allocated to participants at baseline and at follow-up. As the national compendium cost figures give a breakdown of costs for day and residential services in which staff costs are identified, we will be able to adjust the staff cost element to reflect any changes in staff deployment between baseline and follow-up reported. Staff costs are the largest component of costs within day and residential services and arguably most likely to change as a result of treatment (e.g., in comparison with food, lighting, heating, estate, administrative and agency overhead costs).

### Process Evaluation

An instrument to measure the fidelity of the intervention has been developed specifically for this trial. It measures therapists' adherence to the treatment manual and to the principles of cognitive behavioural therapy. In each centre, two sessions will be observed and recorded, by two members of the research team who have no other contact with that centre. The first observation will take place between week 3 and week 6 of the group and the second between week 7 and 10, with at least 3 weeks between the two observations.

## Data analysis

### Quantitative outcomes

The primary analysis will be intention to treat and will compare the mean self-reported PI between the two groups using a two level linear regression model, with participants at level 1 and centres at level 2, with baseline levels of the PI as a covariate. Secondary outcomes will be analysed similarly. Variables will be transformed prior to analysis if necessary to fulfil assumptions of normality.

Formal subgroup analysis of those who are above a threshold of self-reported PI of 1.0 at baseline, and those who meet formal criteria for a diagnosis of 'learning disability', will be undertaken through the fitting of interaction terms to the primary model. Other exploratory analysis will assess whether or not the effect of the intervention differs in different service settings (statutory/independent) and by intellectual and language ability.

A complier adjusted causal effect (CACE) will be estimated using a multi-level mixture analysis [50] to assess the impact of non-compliance with the intervention on the effect shown. A complier will be taken as someone who has attended at least two thirds of the sessions (8 of 12). None of the control group will be able to access the intervention until after follow-up is completed.

The associations between self and key worker/home carer reports will be assessed and compared between intervention and control groups. The association between anger coping skills and outcomes such as provocation, mental health and QoL will also be assessed. Secondary analyses to identify factors predictive of outcomes will be conducted using regression methods, based on the total cohort of N = 180, following delivery of the intervention to the control groups.

### Qualitative outcomes

Service user interviews will be analyzed using Interpretative Phenomenological Analysis (IPA). IPA attempts to reduce the complexity of experiential data through vigorous and systematic analysis in a transparent and plausible manner [51]. It has a specific psychological focus and is suitable for data collected from less articulate/forthcoming participants. The focus of the therapist interviews is on the therapists' personal, subjective experiences and therefore IPA will again be utilised as the most appropriate qualitative analysis.

As the focus of the service manager demands a structured, factual line of enquiry, Thematic Analysis (TA) [52] will be used to categorise participants' responses into themes and sub-themes. Responses will be grouped according to each of the questions posed during the structured interview and will be analysed as such, in order to establish common themes and differences within and between services before and after the intervention. A particular focus of this part of the evaluation will be the perceived influence that the CBT trials have had on professional practice within each of the services.

Both of the qualitative evaluations (IPA and TA) will be subjected to a credibility check, by presenting relevant participants with a summary account of the findings in order to establish whether the analyses have produced an account which is credible and comprehensible to its informants.

### Health economic outcomes

The analysis is directed at addressing three inter-related questions: (a) the extent to which there is added resource usage above support as usual arising from providing the intervention, (b) the extent to which service package costs at follow-up differ from those at baseline, and (c) if both a and b reveal differences in hypothesised directions, the extent to which additional costs might be offset by subsequent savings in ongoing support. (Clearly, it will be redundant to conduct this third stage if the intervention is cheaper to provide than support as usual and results in reduced service package costs or if the intervention is more expensive to provide than support as usual and results in greater service package costs.)

In principle, the cost data will not be treated differently from other data in the analysis. Cost data are frequently skewed. Tests for normality will be applied. If the distribution of data is shown to be non-normal, non-parametric bootstrapping methods will be used to test for differences in costs between groups [53]. Bootstrapping produces a confidence interval for the difference between the means and significance is judged by whether the confidence interval contains zero. Specifically, if the confidence interval does not contain zero, it is assumed that the difference between the means is significant. Bootstrapping does not produce a conventional test statistic by which the level of significance can be judged. Confirmatory, post-hoc, non-parametric testing can be performed to obtain conventional significance levels.

We are primarily reliant on the research to establish associations between the intervention and outcomes including cost. However, we will also attempt to interpret cost changes found. For example, were there to be changes in staff allocation post treatment, we would ask service managers to say what underlay this change, or, if a person moved from living in the family home to an out-of-family placement, we would find out the reason (e.g., did it relate to the person's behaviour or had family capacity to provide care diminished).

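### The bootstrap planned for skewed costs does not carry over the baseline covariate used for other outcomes; adjusting for baseline package cost would be a cheap gain in precision.

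*Protocol article*

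**What the plan says.** The clinical analysis (Data analysis, Quantitative outcomes) uses a "two level linear regression model, with participants at level 1 and centres at level 2, with baseline levels of the PI as a covariate", and adds: "Secondary outcomes will be analysed similarly".

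The cost analysis (Data analysis, Health economic outcomes) starts from the same position: "In principle, the cost data will not be treated differently from other data in the analysis". It then notes that costs are often skewed, plans tests of normality on the data, and gives the route to be taken if they fail: "non-parametric bootstrapping methods will be used to test for differences in costs between groups". The output is described as follows: "Bootstrapping produces a confidence interval for the difference between the means and significance is judged by whether the confidence interval contains zero". That description names no baseline cost, no centre level and no resampling unit.

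Baseline cost information is planned. Under Health-economic evaluation: "All relevant resource use, apart from that at the study sites, will be collected at baseline and at follow-up". The instrument is the CSRI. Resources used at the study sites are logged separately and prospectively. Service managers are also asked for staff-to-service-user ratios at baseline and at follow-up, so that the staff element of cost can be adjusted.

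Under Randomisation, the minimisation factors are the centre's mean baseline self-reported PI, the number of service users recruited, and weekly hours spent with a trainer outside sessions. Cost and residential setting are not among them.

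**The concern.** The article itself expects skewed costs, so the bootstrap is likely to be the cost analysis actually used. At that point the description moves from a model with a baseline covariate to a difference in means with none mentioned. Skewness is no reason to give up the covariate, because a baseline-adjusted difference in mean cost can be bootstrapped on the pound scale just as easily.

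Package costs depend in part on things fixed before randomisation, such as where a person lives and how that setting is staffed. The article recognises that residential settings differ, and its Discussion cites 26% of the variance in residential staff costs as associated with a challenging-behaviour score. With only 30 centres allocated and no cost variable in the minimisation, the arms can differ by chance in baseline cost. An unadjusted follow-up comparison passes part of that difference into the estimate. What is at stake is the precision of the service package comparison, and with it the judgement on whether later savings offset the cost of delivery.

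**Working it through.** **Inputs from the article (Sample size).** 72 analysed per arm, 30 centres (15 per arm), average 6 recruited per centre, 20% loss, ICC 0.11, d = 0.57, p < 0.05 (taken as two-sided), 80% power. After loss, 6 × 0.8 = 4.8 are analysed per centre.

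**Inputs assumed.** The correlation ρ between baseline and follow-up cost and the ICC for cost are not given. I take ρ from 0.3 to 0.9 and borrow the ICC of 0.11, which was chosen for the PI.

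**Step 1: the plan's own figure.**
- Without clustering, n per arm = 2(1.96 + 0.842)² / 0.57² = 48.3, so 49 (50 with the t distribution).
- Design effect = 1 + (4.8 − 1) × 0.11 = 1.418.
- 49 × 1.418 = 69.5 and 50 × 1.418 = 70.9, so 70 to 71 against the stated 72. The figure reproduces.
- It concerns the PI. The article states no power or sample size for cost.

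**Step 2: standard error of an unadjusted difference, in SD units of cost.** √(2 × 1.418 / 72) = √0.0394 = 0.198.

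**Step 3: effect of the analysis choice.** Relative to the unadjusted difference, the variance is multiplied by (1 − ρ²) with baseline adjustment and by 2(1 − ρ) with a change score. This takes equal variances at the two times and a similar correlation within and between centres.

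| ρ (assumed) | Variance factor, adjusted | Variance factor, change score | Adjusted SE | Unadjusted SE ÷ adjusted SE |
|---|---|---|---|---|
| 0.3 | 0.91 | 1.40 | 0.189 | 1.05 |
| 0.5 | 0.75 | 1.00 | 0.172 | 1.15 |
| 0.7 | 0.51 | 0.60 | 0.142 | 1.40 |
| 0.9 | 0.19 | 0.20 | 0.087 | 2.29 |

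The ratio in the last column is 1/√(1 − ρ²), so it does not depend on the borrowed ICC.

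**Step 4: chance imbalance.** The difference between arms in mean baseline cost has a standard error of 0.198 SD among the 72 analysed per arm. Among all 90 recruited it is √(2 × 1.55 / 90) = 0.186 SD, where 1.55 = 1 + (6 − 1) × 0.11. A gap of more than 0.2 SD in either direction therefore has probability of about 0.28 to 0.31. A gap of one standard error (0.198 SD) moves the unadjusted follow-up difference by ρ × 0.198, which is 0.06, 0.10, 0.14 and 0.18 SD at ρ = 0.3, 0.5, 0.7 and 0.9.

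**The case against.** The strongest reply is that the article never calls the bootstrap unadjusted. Bootstrapping is a way to obtain an interval and does not fix the estimator. The section begins by saying that costs are treated like other data, and the PI analysis is also described as a comparison of means although it is baseline-adjusted. A reader might infer that the plan specifies a raw comparison and discards baseline cost. The text does not go that far: it leaves the baseline term unmentioned, and question (b) does compare follow-up with baseline package costs. What remains is that treatment like other data is the default which the fallback replaces, the trigger is the distribution of the data rather than of model residuals, and question (b) does not put baseline cost into the between-group test.

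A second reply is that the analysis may be intended on change from baseline. At high correlation this nearly matches adjustment (variance factors 0.20 and 0.19 at ρ = 0.9). That stands. At ρ = 0.5 it gains nothing over the unadjusted difference, and below 0.5 it is worse.

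A third reply is that a journal article condenses, and that this is a secondary analysis which the authors themselves say is strictly not a technique of economic evaluation. This limits the weight of the point. But the article does describe the fallback method, and the description lacks the covariate it states for the other outcomes.

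Finally, the sizes borrow inputs from the PI calculation and use an assumed correlation. That also stands, although the ratios of standard errors need only the correlation.

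**Conclusion.** The point holds as a cheap improvement. As described, the fallback for skewed costs does not carry over the baseline covariate used for other outcomes, although baseline cost information is collected. The cost is lost precision: an unadjusted standard error about 1.05, 1.15 or 1.40 times the adjusted one at assumed correlations of 0.3, 0.5 or 0.7. At 0.3 the loss is minor.

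A reader might infer that existing cost differences between centres bias the result. They do not: under randomisation the unadjusted difference is unbiased, and chance imbalance is part of its sampling error. Nor are all three economic questions affected alike. Delivery cost, a core part of question (a), has no baseline. The point concerns the comparison of service package costs and what question (c) builds on it. The primary outcome is not touched. No power for cost can be claimed, because the article gives no cost effect, cost ICC or cost correlation.

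**What to change.** In Health economic outcomes, state that when costs are non-normal the between-arm comparison of service package costs is made as follows:

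- In each bootstrap sample, regress follow-up package cost, kept in pounds, on arm and the participant's own baseline package cost. Take the interval for the arm coefficient, which remains a difference in mean cost.
- Build baseline package cost from the baseline CSRI plus, where available, a study-site cost based on the baseline staffing ratios. The CSRI alone is not enough because it excludes study-site resources.
- Resample whole centres within arm, so that the centre level of the main model is kept. If individuals were resampled instead, a nominal 5% test would have a size of 2[1 − Φ(1.96/√DE)]. With 4.8 per centre that is about 7% at a cost ICC of 0.05 (DE 1.19) and about 10% at 0.11 (DE 1.418); both ICCs are assumptions for cost.
- Report intervention delivery cost separately.

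The change costs a sentence or two of wording and a few lines of code, and uses information already planned for collection. The small downside is that participants with missing baseline cost need a simple imputation to stay in the analysis. If adjustment was always intended, the added wording only removes the ambiguity.

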## Discussion

This will be the first multi-centre trial to investigate formally how effectively staff working in services providing day activities for people with learning disabilities are able to use a therapy manual to deliver a CBT-based anger management intervention, following brief training by a Clinical Psychologist. The study incorporates a wider range of outcome measures than previous studies, and includes an analysis of the cost consequences of delivering the intervention. The demonstration that service staff can successfully deliver anger management to people with learning disabilities would have very significant benefits in relation to the current policy of improving access to psychological therapies, by widening the pool of potential therapists, in addition to addressing more effectively an important and often unmet need of this vulnerable client group. Some scepticism has been expressed about whether it is feasible to undertake randomised controlled trials of psychological interventions for people with learning disabilities [54]. The successful implementation of this RCT would serve to allay these doubts and encourage further research to strengthen the evidence base for interventions to support this population. We hope also to identify factors relating to characteristics of participants or settings that are associated with differential outcomes. The study will also pilot a fidelity-monitoring instrument that is not anger specific, but rather, has been designed to be applicable to any CBT-based group therapy for people with learning disabilities.

Felce et al. (2003) found that 26% of the variance in staff costs per person in residential services was associated with scores on a challenging behaviour measure (the Aberrant Behavior Checklist) that we are using as one of our outcome measures [55]. The service-utilization cost and consequences analysis will determine the extent to which delivering the intervention incurs resource inputs over and above support as usual, and whether successful reduction of anger and aggression is associated with any change in subsequent resource use. We rejected a cost utility approach because we believe that the utility-based health state measures such as EQ-5D required for such analyses would not be sensitive to the effects anticipated from the intervention. We rejected a cost effectiveness approach partly because of the multiple objectives of the intervention (e.g. aggression, controllable beliefs, coping, self esteem), which cost effectiveness analysis cannot handle, and partly because the primary outcome measure, the provocation index (PI), is not an effect that features in economic analyses of related interventions. Unless our intervention is shown to be dominant (more effective and less costly than usual care) then an incremental cost effectiveness ratio in terms of extra cost per unit PI would be of little value in informing policy. The proposed cost and consequences analysis is, strictly, not a technique of economic evaluation as it cannot provide a definitive answer to questions of either allocative or technical efficiency. It does however identify the direct and indirect costs (and/or savings) of the intervention and considers these in relation to the range of observed effects.

We anticipate that the qualitative data will enhance the quantitative analyses in four distinct ways. First, as with any well-designed mixed-methods study, we will aim to generate a productive interaction between the quantitative and qualitative analyses: exploratory quantitative analysis will be undertaken to explore possible inter-relationships between factors identified in the qualitative analysis; similarly the qualitative data will be reviewed to explore evidence in relation to findings that emerge from the quantitative modelling. Second, while the quantitative data will provide answers to the question of the effectiveness of the intervention, they will not provide insights into the process or mechanisms of change. This information will, however, emerge from an account of the participants' (both service users and staff) experience of the groups and their understanding of the intervention. The qualitative findings will also influence the interpretation of the outcome data by indicating the personal salience (as distinct from the statistically significance), for clients or those affected by their behaviour, of any changes that are found. And if there are negative results, the qualitative data, alongside the assessment of the fidelity of intervention delivery, may help to explain them. Third, interviewing participants and staff may identify unanticipated outcomes of the group, either positive or negative, and barriers to change. (For example, in a study of anger management by adolescents, qualitative analysis identified some clinically important but unanticipated moderating effects of participants' ages on outcomes, which were confirmed in a reanalysis of the quantitative data: [56].) Finally, if the study shows positive results, the qualitative data, including the impact of the intervention on the culture within day services, will inform the roll-out of the intervention to the wider community.
